### Procedures

#### Overview

Baseline pre-intervention smoking cessation rates will be obtained in all hospitals (intervention and usual care control). Once baseline quit rates are achieved in all hospitals, the Tobacco Tactics intervention will become standard of care for all inpatient smokers in the intervention hospitals only. That is to say, smokers who refuse to participate in the research will still be offered the Tobacco Tactics intervention. Smokers who are not interested in quitting smoking will at least be given brief advice to quit as this is part of the standard of care Tobacco Tactics intervention. Those smokers that are interested in quitting will be offered the complete Tobacco Tactics intervention. To determine population quit rates, all smokers, regardless of whether they are interested in quitting smoking or not, are offered participation in the study, that is, completing the surveys. Smokers in the control sites will receive usual care and be enrolled in the study to determine their quit rates. Changes in pre- to post-intervention quit rates in the intervention sites will be compared to changes in quit rates in the usual care control sites during the same time period.

#### Enrollment of patients into the study

Throughout the pre-training, implementation, and post-training period, smokers in all sites will be identified from the nursing assessment at admission and approached by a research assistant to provide written informed consent as was done in our prior studies [9,10]. See Figure 1 for the recruitment flow chart. Participants will be asked to complete a survey about their smoking habits and other potential moderating variables. Research assistants will also complete a medical record data collection form that includes information such as admission and discharge date and diagnoses, comorbidities, length of stay in the hospital, height, weight, and type of insurance.

**Figure 1 F1:**
[figure not shown]
Recruitment flow chart.

#### Follow-up

A second shorter survey will be sent to the patient 30 days after being recruited to obtain patient perceptions about cessation services received, satisfaction with services, and smoking status. A longer follow-up survey will be sent six months after recruitment to determine longer-term quit rates. A modified Dillman approach [11] will be used to follow smokers. Long-term follow-up response rates for inpatient smoking studies can be low, ranging from 46% to 62% [12,13]. To minimize missing data, as has been done in our prior studies [5], those who do not respond to the mailed surveys and postcards will be called and offered the opportunity to complete the survey by phone with particular emphasis on the dependent variable (quit versus not quit). Participants will be given $10 for each survey. In addition, to corroborate self-reported smoking status six months post-discharge, all participants will be provided a urinary NicAlert cotinine (a metabolite of nicotine) test strip that can be mailed back with the survey. Those who complete the cotinine test will receive an additional $20 for returning the test. In our prior similar VA study, this was found to be a feasible method for obtaining biochemical verification as 90% of those that returned the six-month survey also returned the urinary cotinine test strip. In this way, quit rates in all sites (Tobacco Tactics and usual care) will be established pre- and post-staff training. See Table 4 for a summary of survey measures.

**Table 4 T4:** General measures and time-points

	**Eligibility criteria log**	**Medical records**	**Baseline**	**thirty-day**	**six-month**
**Independent variable**					
Tobacco Tactics intervention versus Usual Care					
**Control variables**					
**Health behaviors**					
· Nicotine dependence (HSI)*			**X**	**X**	**X**
· Alcohol use (AUDIT-C)*			**X**		**X**
**Clinical characteristics**					
· Comorbidities		**X**			
· Depression (PHQ-2)*			**X**		**X**
**Socio-demographics**					
· Demographics (age, sex, race, educational level, marital status, employment, hospital site)*	**X**	**X**	**X**		
**Dependent variables/outcomes**					
**Aim 1: Provider and patient receptivity, barriers, and facilitators to implementation**					
· Face-to-face feedback	**Ongoing**				
· Surveys	**Pre-, post-, and three months post-training**				
**Aim 2: Cessation efficacy**					
· Thirty-day/six-month* reported smoking				**X**	**X**
· Six-month cotinine test*					**X**
**Aim 3: Cost-effectiveness**					
· Cost per quitter			**X**		**X**
· Cost per life-year saved			**X**		**X**
· Cost per quality-adjusted life-year saved (EQ-5D)			**X**		**X**

* These measures/protocols are common to all CHART studies.

#### Implementation of the Tobacco Tactics intervention

Cochrane Collaboration’s Effective Practice and Organization of Care Group found interventions that are more active, such as educational outreach, train-the-trainer models, and the use of opinion leaders were more effective in changing health-care provider behavior [14]. Consequently, a research nurse will implement the Tobacco Tactics intervention in the experimental sites. The primary role of the research nurse is to work with Master Trainers in each site to implement the intervention. Working with the research nurse, the Master Trainers will prepare the facility for dissemination of the intervention including placing the necessary materials on the units, arranging for easy documentation, and identifying nurse champions (preferably one per unit). One incentive for becoming a unit champion may be an opportunity to participate in a leadership role, which may assist with career promotion. The research nurse, along with the Master Trainers, will provide the training sessions on all shifts until all of the staff nurses are trained. An incentive for staff nurses to attend is the opportunity to obtain one Continuing Education Unit (CEU) needed for re-licensure. Based on our prior experience, it may take from two to six months to train the nurses depending on the degree to which the hospital is able to release them from the unit for training.

#### Identification of barriers and facilitators to implementation

Many barriers and facilitators have already been identified in our VA studies and the Trinity System hospitals will benefit from lessons already learned. However, it cannot be assumed that the intervention can be transferred to the Trinity sites without modification of the implementation strategy, and the types of modifications needed are likely to vary by unit and hospital site. Hence, social marketing will be used to identify barriers and facilitators to implementation of the Tobacco Tactics intervention. This focus on the ‘consumer’ (both the nurses who implement and the patients who receive the intervention) involves in-depth research and constant re-evaluation of every aspect of the program. The staff nurses will be surveyed before training, immediately after training, and again three months after the trainings have been completed to identify barriers and facilitators to implementation which will be kept on a log. The barriers and facilitators will be discussed at research team meetings and modifications to the implementation strategy will be suggested. Moreover, patients will be surveyed thirty days after their release from the hospital to determine their satisfaction with the intervention and whether or not they received specific aspects of the intervention. By utilizing social marketing theory and obtaining feedback from providers, the implementation strategy can be modified to maximize ease of delivery.

#### Sustainability

By participating in process evaluation and actually seeing changes made based on feedback given, we experienced in our VA studies and expect to see in this study, that sustainability will be enhanced because nurses can take ownership of the intervention and are therefore more motivated to keep it going. Master Trainers will ensure that the training is incorporated into the orientation for all new nurses. Ease of nurse documentation will be enhanced by use of a cessation services checklist template.

### Description of the Tobacco Tactics intervention (standard of care when all nurses are trained)

#### Tobacco Tactics toolkit for nurses

For nurses, the cessation toolkit includes: 1) one CEU contact hour for training; 2) a PowerPoint presentation on behavioral and pharmaceutical interventions; 3) a pocket card *Helping Smokers Quit: A Guide for Clinicians* developed by U.S. Department of Health and Human Services, Public Health Service; 4) behavioral and pharmaceutical protocols; and 5) a computerized template for nurse documentation. The PowerPoint presentation covers assessment of smokers, behavioral and pharmaceutical interventions, contra-indications for specific groups of smokers, and case studies. The pocket card provides an overview of behavioral and pharmaceutical protocols, which provide guidance for delivering interventions.

#### Tobacco Tactics toolkit for patients

For patients, the cessation toolkit includes: 1) brochure; 2) videotape; 3) manual; 4) 1-800-QUIT-NOW card; 5) pharmaceuticals; and 6) follow-up phone calls. The brochure is one that we created that includes tips for quitting smoking and additional resources to help patients quit. After reviewing many possible videotapes, we selected *Smoking: Getting Ready to Quit* because it was the most appealing and informative one. The video helps smokers develop the skills they need to quit, as well as provides information about smoking cessation medications and dealing with withdrawal symptoms and potential relapse situations. The Tobacco Tactics manual for patients, which has been tested among head and neck cancer patients and veterans, was highly rated by patients, and has been re-illustrated for a more general population. 1-800-QUIT-NOW is a national portal that connects smokers with the state support quitline. As part of usual care, pharmaceuticals may be provided using an algorithm that uses low-risk options first and progresses to higher-risk options depending on the patient’s smoking history, prior experience with quitting, and contra-indications. Providing the brochure, videotape, and manual in advance of cessation counseling and having a set algorithm for medications will save the nurses’ time at the bedside.

#### Nurse counseling

The Tobacco Tactics intervention begins by having the patient watch the fifteen-minute videotape, which is placed on the overhead television to play at least twice a day, preferably at breakfast and dinner time. The nurse will also provide the patient with the Tobacco Tactics manual to look over. At a later point in time, the nurse will meet with the patient for approximately ten to twenty minutes and provide cessation counseling which can be broken into smaller units (for example, four five-minute sessions) and conducted while providing routine care. The cessation program, based on social cognitive theory [15] and Marlatt and Gordon's relapse prevention model [16], incorporates multiple components deemed necessary for a successful program [17], incorporates Agency for Healthcare Research and Quality (AHRQ) recommendations [18] for treatment of smoking, and tailors the intervention to the individual patient’s medical condition and lifestyle. For example, those with low nicotine dependence may only receive behavioral counseling while those with high nicotine dependence may receive both behavioral counseling and medication. The behavioral component of the intervention can be tailored to the patient and, as outlined in the Tobacco Tactics manual, includes: 1) health consequences of smoking; 2) smoker self-assessment; 3) identifying smoker type; 4) change worksheet; 5) money-saving advantage; 6) goal setting; 7) handling thoughts about smoking; 8) assessing high-risk situations; 9) common triggers; 10) coping with cravings; 11) coping with relapses; 12) benefits of quitting; and 13) guided imagery. The pharmaceutical component of the intervention includes a medication protocol used in our prior studies. Pharmacological management will be initiated by the nurse in consultation with the patient’s physician. This will take place just as any discussions between nurses and physicians occur in the context of the providing of health care to patients in the hospital setting. See Appendix A and Appendix B for an outline of the behavioral and pharmaceutical protocols [5].

#### Physician advice

While this is primarily a nurse-delivered intervention, brief physician advice has been shown to enhance quit rates [19]. In our previous VA study, we considered a number of tactics to encourage physician advice including clinical reminders, which were not acceptable to physicians. Based on this feedback, we have had great success coupling a physician reminder for brief advice along with medication sign-off, which once implemented was very sustainable.

#### Telephone counseling

Studies [20-22] have shown that telephone counseling is efficacious to reinforce the initial intervention visit, promote skills building, and monitor pharmacologic treatment. Yet, our experience has been that, due to cost and procedural barriers, telephone counseling is one of the most difficult components of inpatient cessation interventions to implement and sustain. After exploring several unsuccessful options, we have had great success implementing telephone follow-up through Voluntary Services.

Working with the director of Voluntary Services, we will handpick and train volunteers to provide the telephone cessation counseling. Volunteers will be former (at least one year quit) or non-smokers who have good social skills and are interested in providing direct patient care. Volunteer training consists of: 1) participating in the one-hour Tobacco Tactics training program; 2) viewing the video shown to patients about smoking cessation; and 3) viewing a video *Tools for Being a Helpful Peer Partner* about peer support that has been used in other studies [23]. The video demonstrates three types of communication skills: asking open questions; reflective listening; and encouraging efforts to make change. The video helps the individuals understand that when two people share experiences, it can be a very powerful way for them to help each other cope and make good health decisions. The video describes and models Motivational Interviewing (MI)-style communication skills for peer-to-peer communications, explains the basics of MI-style communications, and provides numerous examples of peer-to-peer conversations that use MI techniques.

Using the Tobacco Tactics manual as a guide, volunteers will be given a script that covers three important aspects of providing support to smokers, namely 1) positive reinforcement; 2) handling thoughts about smoking; and 3) strategies to cope with cravings. Volunteers will be supervised making calls until the Master Trainer is comfortable with their performance and they follow the protocol appropriately. Volunteers will provide only behavioral support and refer all medical questions or unanticipated situations/crises to case managers or 911.

There is a documentation template that allows for the nurse to tick off the components of the intervention provided including counseling and medications. If the nurse ticks off on the documentation template that the patient was given the Tobacco Tactics manual, the medical record is programmed to add the patient’s name and phone number to a list that is forwarded to Voluntary Services on a weekly basis. Volunteers then provide peer telephone cessation counseling to patients at two, seven, fourteen, twenty-one, and thirty days after discharge. Since volunteers cannot access or chart in the medical record, paper documentation can be placed in the paper record or scanned into the electronic record by medical records personnel.

#### Fidelity of intervention

Fidelity checks will be conducted by research staff who will observe 5% of staff and volunteers implementing the intervention. These fidelity checks will establish if the components of the Tobacco Tactics intervention are being implemented. Based on these fidelity checks, changes to the implementation strategy may be introduced.

### Description of usual care

The comparison group will receive usual care [24] in accordance to how the hospital responds to current JC standards. Current JC standards require that inpatient smokers with acute myocardial infarction (AMI), congestive heart failure (CHF), community-acquired pneumonia receive adult smoking cessation advice/counseling. Smoking cessation advice/counseling must include at least one of the following: advice to stop smoking, brochures or handouts on smoking cessation, a smoking cessation aid such as nicotine patch, gum, nasal spray, inhaler, lozenge, or sustained-release bupropion, viewed a smoking cessation video [25]. In the Trinity health-care system, all inpatients are screened for smoking and smokers are given advice to stop smoking.

### Measures

The measures for the CHART study group have been described in detail in the overview article and are summarized in Table 4. In brief, the main outcome measures include self-reported thirty-day point abstinence prevalence at six months and biochemically verified abstinence at six months. Additional measures include the Heavy Smoking Index (HSI) for nicotine dependence [26], the Patient Health Questionnaire 2 (PHQ-2) for depression [27], the Alcohol Use Disorders Identification Test–C (AUDIT-C) for alcohol use [28,29], and demographics (age, sex, race, educational level, marital status, employment, hospital site). At thirty-day follow-up, patients are also asked whether they received specific aspects of the intervention and about their satisfaction with the intervention. The EuroQol (EQ-5D) will be used to calculate cost per quitter, cost per life-year saved, and cost per quality-adjusted life-year saved [30].

Additional process measures, some of which will evaluate sustainability, include facility tobacco performance measures, whether or not materials are being used (for example, Tobacco Tactics manuals), whether the Tobacco Tactics training gets integrated into new nurse training, number of follow-up counseling calls made to patients, nurse confidence in delivering the intervention, nurse self-report that they are continuing to implement at three-month post-training, and patient report of, receipt of, and satisfaction with the components of the intervention. Some sample questions include: ‘How confident are you in your abilities to provide smoking cessation services to smokers?’ ranging from ‘Not at all confident’ to ‘Extremely confident’ and ‘Please indicate why you do not expect to provide these services’ with choices of ‘Lack of confidence,’ ‘Not enough training,’ ‘Not enough time,’ ‘Hesitant to upset patients,’ ‘Not my job,’ and ‘Other’. Post-intervention measures will be compared to pre-intervention measures both within and across sites.

### Data analysis

All analyses that compare the two treatment groups will use the intent-to-treat approach in which patients’ data are analyzed based on the treatment intended, not on the treatment actually received. This approach is taken because it is the best method for evaluating the potential effects of disseminating the Tobacco Tactics intervention, which is our focus. Another implication of this approach is that the approximately 25% of patients who are lost to follow-up are included which assures that differences between conditions are not actually due to differential drop out. Extensive follow-up will be conducted including by telephone to minimize the amount of missing data. Statistically justified imputation methods such as multiple imputation will be used to allow analyses including those who have dropped out.

Analyses will adjust for clustering for patients within units using generalized estimating equations (GEE) analyses. GEE is a method of analysis that can account for the correlations among responses from patients in the same cluster [31]. Given the structure of the study with patients nested within hospital units, the hospital unit will be treated as the cluster. The correlation matrix will be of the exchangeable form, assuming the same correlation among any pair of patients in the same hospital unit. This is standard structuring of the matrix for analyzing clustered non-longitudinal data. Given concerns that GEE might be biased with a small number of units, the adjustment for that factor recommended by Morel [32] will be used for each GEE analysis.

There is concern that individual hospitals might differ in factors that influence implementation and effectiveness of the intervention. Though the study would be underpowered to use the hospital as the unit of clustering, several strategies will be used to counter the effects of hospital differences on our finding. If there are baseline differences in the type of patients among the six hospitals, we can control for these differences by adding these variables as covariates in the analysis. If there are multiple differences and we are underpowered to add all of these variables as covariates, we will create a propensity score to control for these differences. Note the quit rates and other factors will be assessed in all hospitals before the intervention is conducted in any of them. Comparison of the post-intervention quit rates to the pre-intervention quit rates (and post and pre levels of other outcomes) is built into the analyses.

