## Methods/Design

### Design

Since many randomized controlled trials have already tested the efficacy of inpatient smoking cessation interventions [1], the real challenge is integrating these interventions into standard of care. Hence, this effectiveness study will use a quasi-experimental design in six Michigan community hospitals of which three will get the nurse-administered Tobacco Tactics intervention and the other three will provide usual care in accordance to how the hospital responds to current Joint Commission (JC) hospital accreditation standards. Implementing the intervention at the facility (hospital) level was the most likely design to remain sustainable once the study was completed.

Throughout the entire study, smokers are surveyed at baseline, thirty days and six months post-recruitment. In this way, quit rates at two time points for all patients are determined during intervention (of less interest), and post-intervention in both the Tobacco Tactics and usual care groups. There are two sources of control. The first source of control is pre- versus post-intervention changes within hospitals; this source of control will NOT control for seasonal changes. The second source of control is changes in the Tobacco Tactics sites compared to the usual care sites; this source of control WILL control for seasonal changes and any other historical events that may influence quit rates across sites.

The quasi-experimental design allows for implementation in natural environments minimizing threats to external validity as natural environments do not suffer the same problems of artificiality as compared to a well-controlled laboratory setting [7]. While quasi-experimental designs are more feasible, the lack of randomization at the patient level may pose many challenges in terms of internal validity making it hard to rule out confounding variables [8]. To minimize the effect of confounding variables, the six hospitals have been split into two groups of three that as a group are matched on hospital size and percentage of minority patients. While we could have arbitrarily decided which group of three hospitals gets the intervention and which does not, we wanted to reduce investigator bias and used a computerized coin flip to assign the groups to experimental and control conditions. See Table 1 for the overall study design.

**Table 1 T1:** Overall study design

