We anticipate a quit rate of 30% in the hospitals receiving the Tobacco Tactics intervention and 20% in the usual care hospitals. However, to assure that these differences are not just due to differences between the hospitals, a GEE analysis will be conducted using the logit link function with the hospital unit as the definition of the cluster analogous to moderated logistic regression analysis in which quitting is predicted by time frame (baseline versus intervention period), intervention group (Tobacco Tactics versus usual care), and the product of those two variables. The statistical significance of the product will indicate that the difference between the Tobacco Tactics and the usual care comparison sites depends on whether or not the intervention has been implemented. We anticipate no difference between the sites at baseline, but a notable difference after the interventions have been implemented.

In addition, harm reduction will be compared between the two groups by analyses of number of cigarettes smoked per day, number of quit attempts, and nicotine dependence (as indicated by Fagerstrom test). For each of these analyses, the same general approach taken to the primary dependent variable will be applied including: descriptive statistics on baseline and intervention period and a GEE with the hospital unit as the definition of the cluster analogous to moderated regression analysis to compare the differences between the sites (Tobacco Tactics versus usual care) by time (baseline versus intervention period). Both the descriptive statistics and the significance tests differ for these other outcome measures because of their different distributions (that is, normal or not). Count variables will be analyzed assuming a Poisson distribution using a log link function while the Fagerstrom test scores will be modeled with an identity link function since it is normally distributed.

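### Patient-level adjustment of the primary group-by-period model is optional and depends on finding differences among hospitals, so changes in patient mix between periods can go unadjusted

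*Protocol article*

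**What the plan says.** The primary analysis (Aim 2) is a GEE with logit link, clustered by hospital unit. Its terms are given as follows: "quitting is predicted by time frame (baseline versus intervention period), intervention group (Tobacco Tactics versus usual care), and the product of those two variables". No patient covariate and no hospital term is named. The target is a difference in differences; the Procedures overview says "Changes in pre- to post-intervention quit rates in the intervention sites will be compared to changes in quit rates in the usual care control sites".

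Enrolment is continuous: "Throughout the pre-training, implementation, and post-training period, smokers in all sites will be identified from the nursing assessment at admission". The before and after groups are therefore different patients.

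The Data analysis section states two rules for patient-level adjustment. The first is "If there are baseline differences in the type of patients among the six hospitals, we can control for these differences". The second is a fallback: "If there are multiple differences and we are underpowered to add all of these variables as covariates, we will create a propensity score". Neither says what counts as a difference or which variables are eligible.

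Table 4 separately lists control variables: nicotine dependence, alcohol use, comorbidities, depression, and demographics that include hospital site. All are collected at baseline, from medical records or on the eligibility log. Nothing in the text ties this list to the Aim 2 model. The Design section concedes that "the lack of randomization at the patient level may pose many challenges in terms of internal validity making it hard to rule out confounding variables".

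**The concern.** In a difference in differences on repeated cross-sections, the group term absorbs a patient-mix difference between the arms that stays constant over time. Two things are not absorbed:

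- a change in patient mix that differs between the arms from before to after;
- a change in how much each hospital contributes to its arm's recruitment, because the model has a group term but no hospital term.

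A comparison of patient types among six hospitals does not look for the first and addresses the second only in part. It can prompt adjustment where the product is unbiased and fail to prompt it where the product is biased.

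The rule is also permissive and has no criterion. Whether the primary result is adjusted, and for what, would be settled after the data are seen. In a non-randomised comparison of two groups of three hospitals, that leaves the main conclusion open to choice.

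**Working it through.** The plan gives no figure for this point, so there is none to reproduce. Its sample size of 2,350 is used below only to set cell sizes.

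**Inputs from the protocol article.** Quit rates 30% v 20%, a planned difference of 10 points (Power analysis; Aim 2); total 2,350 (Power analysis); minority shares of 70% and 4% at Hospitals 1 and 2 (Table 3).

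**Assumed inputs.** Quit rates by nicotine dependence, and the size of any change in mix. The documents give neither, so a range is shown. There is no true intervention effect in steps 1 to 4.

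**1. Simple illustration.** Bias in the product on the risk scale = change in mix in one arm × difference in quit rate = 0.10 × 0.15 = 0.015. That is 1.5 points, or 1.5/10 = 15% of the planned effect.

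**2. Stable difference.** The low-dependence share is 60% in intervention hospitals and 40% in usual care, in both periods, with quit rates of 30% (low dependence) and 15% (high dependence).
- Intervention, both periods: 0.6 × 0.30 + 0.4 × 0.15 = 0.24.
- Usual care, both periods: 0.4 × 0.30 + 0.6 × 0.15 = 0.21.
- Product: odds ratio 1.00, no bias. The hospitals differ, so the rule would prompt adjustment.

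**3. Change in one arm only.** The low-dependence share is 50% everywhere before, and rises afterwards in intervention hospitals only. With 30%/15% and a rise to 60%:
- Before, and usual care after: 0.5 × 0.30 + 0.5 × 0.15 = 0.225.
- Intervention after: 0.24.
- Product odds ratio: (0.24/0.76)/(0.225/0.775) = 1.09.

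A check of the pre-intervention period would find nothing. Across the range:

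| Assumed quit rates (low/high dependence) | Share after 60% | Share after 70% | Spurious points |
|---|---|---|---|
| 25%/15% | OR 1.06 | OR 1.13 | 1 to 2 |
| 30%/15% | OR 1.09 | OR 1.18 | 1.5 to 3 |
| 35%/10% | OR 1.15 | OR 1.31 | 2.5 to 5 |

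The planned effect is (0.30/0.70)/(0.20/0.80) = OR 1.71.

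**4. False-positive rate.** This was simulated with 1,000 runs, 2,348 patients in four equal cells and no clustering. The Monte Carlo standard error at 5% is √(0.05 × 0.95/1000) = 0.7 points.

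| Scenario | Unadjusted | Covariate always included |
|---|---|---|
| Stable 60% v 40%, rates 30%/15% | 5.7% | 5.7% |
| Stable 60% v 40%, rates 35%/10% | 4.5% | 4.4% |
| Change to 65% in one arm, rates 30%/15% | 9.5% | 4.2% |
| Change to 65% in one arm, rates 35%/10% | 19.3% | 5.5% |

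**5. Recruitment shares.** If 10% of Group 1's recruitment moved from Hospital 2 to Hospital 1 between periods, that arm's minority share would change by 0.10 × (0.70 − 0.04) = 6.6 points, taking the Table 3 shares to hold among enrolled smokers. The Aim 2 model has no term to absorb this.

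**The case against.** The strongest reply is that adjustment is foreseen. Table 4 labels its control variables without any condition, the Data analysis rule is aimed at hospital differences, and an article may leave the final covariate list to an analysis plan. The Measures section also closes by promising comparisons of measures before and after, within and across sites. In addition, Table 4 uses the word baseline for each patient's enrolment survey, so the trigger need not be confined to the pre-intervention period.

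Part of this stands: the article does not ignore adjustment, and the word baseline is ambiguous. But the Measures sentence follows the process measures, and neither it nor the Table 4 label puts a covariate into the Aim 2 model. The conditional rule is stated, not merely left out. On either reading of baseline, the contrast is among hospitals, not arm by period.

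Several stronger readings are tempting, and the documents do not support them:

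- **That season confounds the product.** The concurrent usual-care hospitals handle a seasonal change common to both arms. Only an arm-specific change matters.
- **That the trigger looks at the wrong contrast altogether.** Hospital differences do matter if recruitment shares shift. The trigger is incomplete.
- **That precision is being lost.** On the logit scale, adding a prognostic covariate raises the standard error of the product slightly (0.193 to 0.197 for 30%/15%; 0.193 to 0.203 for 35%/10%; unclustered) while the estimate moves from marginal to conditional. The gain in power is only about 2 and 6 points.
- **That a propensity score has no basis at this sample size.** Expected quitters are 0.225 × 1,762 = 396 (after 25% loss) to 0.225 × 2,350 = 529, or 20 to 26 per parameter for an assumed 20 parameters. This ignores clustering and counts patients recruited during implementation. The unclustered requirement is 588, and 2,350/588 = 4.0. If that were all design effect, effective quitters would be 588 × 0.225 = 132, or 6.6 per parameter. That is a lower bound, but enough to leave the fallback defensible.

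**Conclusion.** The point holds as a weakness in a stated rule. Adjustment of the primary model is optional, has no criterion, and depends on a comparison that does not cover the two ways in which patient mix can bias the product. It also leaves the choice of adjusted or unadjusted result until after the data are seen.

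The mechanism follows from the design described. The size does not. The 1.5-point figure, the 1 to 5 points in the table and the false-positive rates rest on assumed quit rates by dependence and an assumed one-arm change in mix, and the simulation ignores clustering. A reader might infer that the trial's result will be biased. The documents do not show that such a change will occur, only that the plan does not guard against it. The change is worth making because the comparison is not randomised at patient level and the remedy is cheap.

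**What to change.** Amend the Data analysis rule and the Aim 2 model description as follows.

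- Include the Table 4 control variables in the primary GEE whatever differences are observed: HSI, AUDIT-C, PHQ-2, comorbidities, age, sex, race, education, marital status and employment. Use baseline values only, because HSI, AUDIT-C and PHQ-2 are also measured after the intervention.
- Enter hospital as a fixed effect. This absorbs the group main effect; the group-by-period product stays estimable.
- Report the unadjusted product alongside, and tabulate baseline patient mix by arm and period.
- Remove the conditional wording. A propensity score built from the same prespecified variables may stay as a sensitivity analysis.

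The cost is mainly wording, since all the variables are already collected. There are two small downsides: missing baseline covariates must enter the imputation already planned, and the adjusted odds ratio is conditional rather than marginal, so it will differ somewhat from the unadjusted one even without confounding. The report should say so.
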